## Abstract

**Background:**

The search for preventive methods to mitigate functional decline and unwanted relocation by older adults living in the community is important. Preventive home visit (PHV) models use infrequent but regular visits to older adults by trained practitioners with the goal of maintaining function and quality of life. Evidence about PHV efficacy is mixed but generally supportive. Yet interventions have rarely combined a comprehensive (biopsychosocial) occupational therapy intervention protocol with a home visit to older adults. There is a particular need in the USA to create and examine such a protocol.

**Methods/Design:**

The study is a single-blind randomized controlled pilot trial designed to assess the feasibility, and to obtain preliminary efficacy estimates, of an intervention consisting of preventive home visits to community-dwelling older adults. An occupational therapy-based preventive home visit (PHV) intervention was developed and is being implemented and evaluated using a repeated measures design. We recruited a sample of 110 from a population of older adults (75+) who were screened and found to be at-risk for functional decline. Participants are currently living in the community (not in assisted living or a skilled nursing facility) in one of three central North Carolina counties. After consent, participants were randomly assigned into experimental and comparison groups. The experimental group receives the intervention 4 times over a 12 month follow-up period while the comparison group receives a minimal intervention of mailed printed materials. Pre- and post-intervention measures are being gathered by questionnaires administered face-to-face by a treatment-blinded research associate. Key outcome measures include functional ability, participation, life satisfaction, self-rated health, and depression. Additional information is collected from participants in the experimental group during the intervention to assess the feasibility of the intervention and potential modifiers. Fidelity is being addressed and measured across several domains.

**Discussion:**

Feasibility indications to date are positive. Although the protocol has some limitations, we expect to learn enough about the intervention, delivery and effects to support a larger trial with a more stringent design and enhanced statistical power.

**Trial Registration:**

ClinicalTrials.gov ID NCT00985283

## Background

The current state of affairs in population aging and gerontology in the USA and abroad set the stage for this study protocol. While an extraordinarily large cohort of the population is moving into the latter phases of life, the resources to fund both acute and long term care for that cohort are in question. Gerontological research suggests that this cohort will want to remain at home and their well-being can best be maintained by doing so [1,2]. At the same time, an emerging understanding of older adult well-being suggests that domains of activity, participation, and overall engagement with life are essential. In light of these circumstances, there is a distinct need to develop a solution that will enhance the well-being of older adults in these domains and allow them to stay at home longer as well as remain functional, relatively healthy and satisfied. The project described here intends to begin the process of addressing these needs by testing an intervention termed *preventive home visits *(PHVs).

The USA and other countries are confronted with the responsibility of not only taking care of the growing population of older adults who become sick or frail but also helping those who are not yet in need of care to maintain their independence and well-being. Effective prevention could produce health care cost savings as well as improve the lives of older adults and their families. A particular goal of prevention in the older population, therefore, is providing older adults the ability to remain in their own home and community instead of entering the formal care system. As aging progresses, the probability of frailty or sickness, and thus separation from home, increases. Such separation can be traumatic for older adults. On the other hand, the ability to remain at home can help an older adult maintain mental and physical health through engagement in daily activities—such as housekeeping or social interactions—if adaptations to the aging process can be learned and used.

The argument here is two-fold. First, the gerontological evidence is strongly suggestive that a positive outlook on life (e.g., affect, happiness, optimism) can enhance mental and physical well-being [3]. Second, the ability to engage mentally, socially, and physically with the world from a community setting can positively affect both sides of the outlook and health equation [4-8]. Moreover, extending independence and participation for older adults can have important positive consequences for others. Informal caregivers (e.g., children of older adults) carry a large burden and suffer their own negative health consequences when older adults become frail and ill [9]. A program that could affect older adults and their family and care networks would extend beyond the issue of individual betterment to community improvement. To be able to sustain or improve participation, function, and social interaction within the context of aging in one's own home and community setting is therefore an admirable and compelling goal.

Based on systematic reviews and meta-analyses, evidence about effectiveness is mixed but supportive enough to suggest continued research. The first comprehensive review of programs similar to preventive home visits was conducted by Stuck and Siu [10] who concluded that comprehensive geriatric assessment (CGA) programs were associated with statistically significant higher odds of living at home at follow-up. In a similar review of 21 randomized controlled trials of "health assessments" Byles [11] concluded that such interventions were associated with improved health outcomes for older adults but that specific mechanisms for those associations were difficult to identify. Van Haastregt and colleagues [12] focused their systematic review more specifically on 15 studies of preventive home visits. Although the authors noted substantial differences among the interventions, samples, and outcome measures and that visits were more often than not tailored to the needs of participants in the studies reviewed, they concluded that there was no clear evidence for the efficacy of such visits. In another systematic review soon after, Elkan et al. [13] criticized van Haastregt and colleagues for not pooling the results of the studies they reviewed. The results of their 15 study meta-analysis focused on preventive home visits by trained nurses and suggested that they are associated with a decrease in mortality and a reduction in admissions to long term care institutions. Assessing multidimensional preventive home visit programs since 2000, Huss et al. [14] concluded that such programs have positive effects on mortality rates, functional decline, and nursing home admissions, especially in younger old groups (77 or younger). A large study in Denmark using pre-existing home visit programs in 34 municipalities with over 4000 older people established that an educational intervention used with the home visits (to improve skills, interdisciplinary collaboration and reduce ageism among providers) had the positive outcomes of improved functional ability and cost neutrality [15,16].

The one systematic review of 17 occupational therapy interventions for community dwelling older people [17] argues that such interventions result in various positive outcomes. The types of interventions reviewed included comprehensive OT interventions (outside the home), training of skills combined with instruction on assistive devices, instruction only regarding assistive devices, and counseling of primary care providers. Most outcome measures used in the reviewed studies focused on activities of daily living or functional independence measures, and only a couple used measures of well-being (e.g., life satisfaction) or general health outcomes (e.g., the MOS 36-Item Short-Form Health Survey SF-36). The one comprehensive OT intervention study that was of high quality and with positive results [18,19] used outcome measures for participation, function, life satisfaction, and health. More recently, Gitlin and colleagues [20] have suggested the feasibility of in-home OT-based prevention for older people with dementia and their caregivers. Our study builds on this evidence base for interventions outside the home and Gitlin and colleagues' suggestion of the feasibility of an in-home, OT-based preventive intervention.

### Aims and hypotheses

We developed our approach using the research literature as well as principles of Danish preventive home visits [21]. We also used a conceptual framework synthesized from (a) the World Health Organization's (WHO) International Classification of Functioning, Disability, and Health, or ICF as it is widely known [22] and (b) the American Occupational Therapy Association's (AOTA) practice framework [23] (see Figure 1). Common in those frameworks is the perspective of *positive *function, aging, and participation. The primary aims were to (a) determine if the PHV intervention used in the proposed project is feasible in the USA context, (b) estimate the effect of a PHV intervention on functional ability, (c) ascertain if the PHV intervention causes improved psychosocial outcomes that relate to well-being, and (d) estimate the effect of the intervention on health outcomes. Accordingly, we used hypotheses such as the following examples to structure the measurement and analysis of outcomes: (*H*_1_) the experimental group will exhibit greater (more positive or less negative) functional ability across the study period than the comparison group, (*H*_2_) the experimental group will show a significantly better slope for life satisfaction across the study period than the comparison group, and (*H*_3_) the experimental group will have significantly lower rates of referral to rehabilitation, skilled nursing or assisted living facilities than the comparison group.

**Figure 1 F1:**
[figure not shown]
**Conceptual framework for preventive home visits study**.

## Methods/Design

The study goals are to assess the feasibility, and to obtain preliminary efficacy estimates, of an occupational therapy-based preventive home visit (PHV) intervention for community-dwelling older adults. To achieve these goals, a single-blind randomized controlled pilot trial using a repeated measures design is employed. Community-living (not in assisted living or a skilled nursing facility) older adults (75+) in one of three central North Carolina counties found to be at-risk for functional decline were eligible for the study. Participants who consented were randomly assigned to an experimental or a comparison group. Over a 12-month follow-up period, the experimental group receives 4 preventive home visits while the comparison group receives a minimal intervention of mailed printed materials. Pre- and post-intervention questionnaire measures are administered face-to-face by a treatment-blinded research associate. Additional information is collected from participants in the intervention group during the intervention to assess the feasibility of the intervention and potential modifiers. The protocol was approved by the Public Health/Nursing Institutional Review board of the University of North Carolina at Chapel Hill. Written informed consent is used with all participants.

### Recruitment and randomization

We recruited the sample through several concurrent methods: senior center and clinic flyers, email to community-based lists, community presentations, random phone calls to those on local senior center rosters, and announcements via local aging service providers. For those who consented to continue through the recruitment process, we used the Vulnerable Elders Survey (VES) [24] to determine at-risk participants for inclusion in the study. To ensure that treatment groups were balanced on important potential confounders, we used permuted-block randomization within strata defined by VES scores (3-4 or 5+), ethnicity (non-Hispanic white or minority), and residential status (living alone or not) (see Table 1). The recruitment and allocation is further illustrated in Figure 2.

**Table 1 T1:** Measurement process.

CONSTRUCTS	OPERATIONALIZATION	**TIME COLLECTED**^**#**^									
		**S**	**O**_**1**_	**I**_**1**_	**O**_**2**_^*****^	**I**_**2**_	**O**_**3**_	**I**_**3**_	**O**_**4**_^*****^	**I**_**4**_	**O**_**5**_

**Screening for Inclusion**											

Vulnerability	Vulnerable Elders Survey (VES)	X									

**Blocking/Randomizing**											

VES score	3-4, 5+	X									
Ethnicity	White, other		X								
Living arrangement	with someone, alone		X								

**Outcomes**											

*Primary Outcomes*											
Functional ability	Late Life Function & Disability Instrument		X		X		X		X		X
Participation	Late Life Function & Disability Instrument		X		X		X		X		X
Occupation	self-assessed performance and frequency			X		X		X		X	

*Secondary Outcomes*											
Life satisfaction	Satisfaction with Life Scale		X		X		X		X		X
General health	SF-12 v.2		X		X		X		X		X
Depression symptoms	CESD-10		X		X		X		X		X

*Tertiary Outcomes*											
Acute care utilization	frequency, duration		X		X		X		X		X
Rehab or longer term care	frequency, duration		X		X		X		X		X

**Covariates^**											

*Demographics*											
Age	years		X								
Gender	male, female		X								
Ethnicity	White, African Amer., Hispanic, Asian, oth		X								
Education level	years completed		X								

*Environment of the Home*											
Type of dwelling	single family, duplex, apt., mobile, other		X								
Location of dwelling	city, suburban, rural		X								
Problems with steps	none, minor, moderate, major			X							
Problems with indoor lighting	none, minor, moderate, major			X							

*Social/Cultural Context*											
Living companion	alone, spouse, child, other etc.		X								
Knows neighbors	well, somewhat, little, no contact		X								
Interaction with family	days per week			X							
Importance of spirituality/religion	very, somewhat, not			X							

*Health & Function*											
Self-rated energy level	low (1) - high (5)			X		X		X		X	
Pain	low (1) - high (5)			X		X		X		X	
Fall frequency	number of falls in past 4 months			X		X		X		X	
Cognitive function	6-Item Cognitive Impairment Test		X		X		X		X		X

*Community Mobility*											
Accessing community	frequency; purpose			X							
Driving status	yes, with limits, ceased			X							
Public transportation	availability; use; type			X							

*Adherence to recommendations*	to all, to roughly half, to none					X		X		X	

**Fidelity Dimensions**		**P**									

Created manual		X									
Protocol manual training for OTs	checklist for competence	X									
Clinical/case meetings	maintaining reliability of intervention				X		X		X		
Intervention Delivery Checklist	administers protocol as trained? (Yes, No)			X		X		X		X	
Participant exit interview	participant perceptions of intervention and own behaviors vis-à-vis recommendations										X

^# ^P = pre-study, S = screen for inclusion, O = measurement occasion by researcher, I = intervention delivery and data collection by OT

* Observations conducted by telephone

^ Constructs listed under these categories are examples and not inclusive of all being measured

**Figure 2 F2:**
[figure not shown]
**Participant flow chart**.

### Procedure

#### Experimental group

The intervention is a structured protocol that leaves room for flexibility based on the older adult and his or her situation, preferences, and needs. Therefore, it is uniform in terms of the domains that are evaluated by the visiting occupational therapist (OT), but the recommendations are individualized (tailored) for each participant. Core domains covered in each visit include (a) physical environment of home and surroundings, (b) social/cultural context, (c) performance and participation in occupations, (d) health and functional concerns affecting participation, and (e) community mobility issues affecting participation. At each PHV, the occupational therapist makes sure that all domains are covered before leaving the participant's home, but the structure of the visit may vary because we believe it is essential for the therapist to listen actively to the participant and let the participant lead the direction of the conversation and activity to areas important to her or him. The visit is a collaborative effort and the participant is encouraged to be as active as possible in identifying both health promoting activities and problem areas. The OT and the participant work together to develop solutions. Before leaving, the OT reviews the list of issues and health promoting activities with the participant and describes in general terms which areas the recommendations will address. After the visit, the OT generates up to 5 detailed key recommendations and shares them with the subject via mail. The second through fourth visits are additional assessments with more focus on how the recommendations have worked, changes in the participant's situation, and what recommendations are needed at that point.

#### Comparison group

In order to be able to attribute treatment effects to the tailored and OT-delivered PHV intervention, we use "attention" control, i.e., a generic, minimal intervention providing nonspecific attention and support by non-occupational therapy personnel. This minimal intervention consists of a mailed information packet about local services for older adults as well as information on fall prevention from the Centers for Disease Control and Prevention. The intervention was devised because it is a low cost program that any local Department on Aging or senior center should be able to offer to community dwelling older adults.

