## Discussion

The potential limitations of the study are several. Although logically sound based on the literature and our experience with older adults, our protocol has not been proven feasible or effective, and this project will provide a good initial test. One potential challenge to analysis is that the intervention is delivered as a bundle, and that makes it difficult to pinpoint the cause of any effects. We believe that the embracing of complexity in older adults' lives is worth this limitation, however, and we are collecting detailed data through the PHV instrument to help us parse out effects. An additional limitation of our intervention is that it does not address directly the physical health limitations of older adults. Because the intervention is not a medical approach, we are not able to, nor are we attempting to, directly (medically) assist older adults with physical ailments. The visiting OT does, however, refer an older adult to medical care (or contact the appropriate agent about such need) if an older adult is experiencing acute health or safety problems or is clearly at-risk for near-term adverse health consequences due to a mental, physical or social problem. Because of budget constraints and the need to increase statistical power, a study design providing more interpersonal contact with the experimental group is potentially confounding. This was a compromise we found acceptable at this stage of the protocol's development and assessment. Future studies will balance group contact as well as group covariate measurement to allow for more stringent tests of effects.

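### The mailed-packet comparison arm is called an attention control that permits attribution to the tailored OT visit, but the design does not match contact and the Discussion concedes this

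*Protocol article*

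**What the plan says.** All references are to the protocol article.

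- **Comparison group**, purpose of the control: "In order to be able to attribute treatment effects to the tailored and OT-delivered PHV intervention, we use 'attention' control". It is defined there as "a generic, minimal intervention providing nonspecific attention and support by non-occupational therapy personnel".
- **Comparison group**, content: "This minimal intervention consists of a mailed information packet about local services for older adults", together with fall-prevention information from a public agency. The reason given for devising it is that "it is a low cost program that any local Department on Aging or senior center should be able to offer".
- **Methods/Design**, contrast between arms: "the experimental group receives 4 preventive home visits while the comparison group receives a minimal intervention of mailed printed materials".
- **Experimental group**, nature of the visits: the authors hold that "it is essential for the therapist to listen actively to the participant and let the participant lead the direction of the conversation".
- **Discussion**, limitation: "a study design providing more interpersonal contact with the experimental group is potentially confounding". The authors explain this by budget and power, accept it as a compromise at this stage, and add: "Future studies will balance group contact as well as group covariate measurement to allow for more stringent tests of effects".
- **Analysis plan**: the pilot's efficacy estimates help to decide whether a larger trial is justified and how large it should be. They also partly determine which outcome becomes its primary one.

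**The concern.** An attention control supports attribution to specific content only if it holds non-specific contact roughly equal between arms. The Comparison group section claims that function, then describes a mailing. A reader who classifies the comparator from that section would take a positive result as evidence for tailoring by an OT, when contact alone could have produced some or all of it.

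The outcomes make this a practical matter. The LLFDI, Satisfaction with Life Scale, SF-12 and CES-D 10 are questionnaire measures answered by the participant, and life satisfaction, depressive symptoms and social participation could plausibly respond to regular visits from an attentive professional. The blinding described is that of the research associate. The article does not say in so many words that participants are unblinded, but they will know whether a therapist comes to their home.

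The pilot estimate is also to be carried forward. If a later trial balances contact, as the Discussion intends, it will estimate a different contrast from the one estimated here. Choosing its primary outcome partly on pilot efficacy could also favour whichever outcome responds most to contact.

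**Working it through.** The plan gives no figure for contact or for its effect, so there is none to reproduce on this point. Its only design figure, 80% power for 0.5 SD with 120 participants, does not enter the argument. The check is a count from Table 1, a comparison of sections, and a short statement of what the contrast estimates.

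**1. Planned contact by arm, after screening (Table 1 and its footnotes).**

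| | Experimental | Comparison |
|---|---|---|
| Assessments by the research associate, O1 to O5 | 5 | 5 |
| of which by telephone (O2, O4) | 2 | 2 |
| In-person assessments (O1, O3, O5): 5 − 2 | 3 | 3 |
| OT home visits, I1 to I4 | 4 | 0 |
| **In-person occasions** | 3 + 4 = **7** | 3 + 0 = **3** |
| Occasions of any kind | 5 + 4 = 9 | 5 + 0 = 5 |

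The in-person count is the relevant one; 9 versus 5 includes the telephone assessments. The difference is four therapist visits either way. The assessments are common to both arms and are not described as part of the control intervention, so they do not close the gap.

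**2. Measurement by arm.** Table 1 places energy, pain, falls and several home and social items at the OT visits, and the Primary outcomes section says that occupation is measured in the experimental group only. The experimental arm is therefore questioned more often, and about more things. The Discussion's promise to balance covariate measurement later acknowledges this.

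**3. Claim against description.**

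| Needed for the attribution claim | What the article describes |
|---|---|
| Comparator delivers attention and support | A mailing, with no call, visit or conversation |
| Comparator chosen to match contact | Chosen for low cost and ease of local delivery |
| Contact balanced in this trial | Imbalance conceded; balancing left to future studies |

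**4. What the contrast estimates.** Write the expected difference between arms, assuming for simplicity that the parts add, as

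D = content + contact + measurement,

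where *content* is the effect of tailored, OT-delivered advice beyond that of the packet, *contact* is the effect of four attentive visits as such, and *measurement* is the effect of the extra questioning. The trial supplies one estimate, of D. It has no arm in which contact or measurement varies without content, so the three terms cannot be separated. A trial that balanced contact and measurement would estimate *content* alone. If contact + measurement is positive, D exceeds that target by exactly this amount; if it is zero, D does not exceed it. The documents say nothing about which holds.

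**The case against.** The strongest reply is that the article already discloses the problem. The Discussion names the contact imbalance, gives the reasons for it and promises balanced contact and measurement later. It also says that bundling makes the cause of any effect hard to identify. The Abstract and Methods/Design describe the comparator plainly as printed material sent by post, so no reader is misled about what was delivered. This stands, and it lowers the consequence. It does not correct the Comparison group section, which still states the opposite property as the reason for the design.

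A second reply is that the sentence may mean attribution to the intervention as a whole. On that reading randomisation against any comparator would do, and the attention label would add nothing. Defining the control as attention from non-OT staff makes sense only if attention is meant to be held constant. The sentence needs correcting on either reading.

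Three stronger readings are tempting and are not supported:

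- *The comparator is wrong.* A minimal comparison is legitimate in a pilot. The fault is in its label and in the claim made for it.
- *The imbalance is concealed.* The Discussion states it.
- *The pilot estimate will be too large by a calculable amount.* A reader might assume that contact alone is worth 0.1 to 0.2 SD, subtract this from the 0.5 SD planning target, and arrive at about 100 to 176 per arm instead of 64 (two-sided 5% level, 80% power). The contact effect is pure assumption, and 0.5 SD is a planning target, not a pilot result. The Analysis plan itself warns that the estimates will be imprecise and may lead to revised projections. Overstatement is possible, but neither its presence nor its size can be derived from the documents.

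**Conclusion.** The point holds as a contradiction between sections and an attribution claim that the design cannot support. The comparison arm is a mailing, planned in-person occasions are 7 against 3, and the Discussion itself treats the difference in contact as a possible confounder. The supportable conclusion concerns the whole preventive home visit package against mailed information.

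This rests on the text and on Table 1 as planned. It assumes that the packet is the entire control intervention, as the article describes it, and that O1, O3 and O5 are in person, which follows from the telephone footnote and the face-to-face administration stated in Methods/Design. For a later contact-balanced trial, the pilot estimate may overstate the available effect; no magnitude is claimed. The correction is worth making because it changes what the trial may conclude. It does not affect the validity of the randomised comparison itself.

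**What to change.** 1. In the Comparison group section, remove the attention label and the attribution clause, and call the arm a mailed minimal-information comparison. Suitable wording: *The comparison group receives a mailed packet of general information. The trial compares the whole preventive home visit package, including therapist contact and data collection at visits, with that packet. It does not separate tailored content from contact.*
2. Limit the efficacy conclusion to that contrast, in line with the Discussion.
3. Where the pilot estimate is used to justify or size a contact-balanced trial, or to choose its primary outcome, state that it includes any non-specific contact effect and may therefore overstate the effect available there. Do not attach a numerical discount, since none can be derived from the documents.

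No new data, visits or analyses are needed, and the change remains possible with enrolment complete. The price is a narrower causal claim.
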